### Week 4 visit

2.5

After four weeks on the study medication, participants will come to the Center for Clinical Investigation (CCI) for a blood draw. Participants will be asked to fast after midnight before the morning blood draw. Laboratory measurements are specified in **Table 5**.

**Table 5 T5:** Week 4 tests.

Blood Draw (Week 4) Study Tests	
Complete Blood Count with differentials	FABP4, NEFA, Glycerol
Comprehensive Metabolic Panel	EDTA Plasma
Hemoglobin A1c, Insulin, C-Peptide, Glucagon	RNA from PBMC
hs-CRP, TNFa, IL-6	Lipid Panel, Standard Triglycerides Total Cholesterol HDL Cholesterol LDL Cholesterol (Direct) Cholesterol/HDL Ratio (Calculated), Non-HDL Cholesterol (Calculated)
Total Adiponectin, Leptin	

### Statistical analysis

2.6

#### Statistical methods

2.6.1

We will use a paired t-test for the primary endpoint as we measure insulin sensitivity M and M/I values from the same individuals before and after taking POA vs placebo. However, given the relatively small sample size of the study, which raises the possibility of results not being normally distributed, we will also use Wilcoxon non-parametric test to compare two paired groups (before and after, POA vs placebo). The focus of these analysis will be insulin sensitivity; however, we will use multivariate regression analysis, which also provides the flexibility of controlling for and evaluating covariates such as age, sex, sleep, and BMI. We will apply the same testing to all endpoints. According to some association studies, we expect to see a higher magnitude of the POA effect in women. We will aim for study enrollment to be at least 50% women to be able to detect sex differences in the POA effect.

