### Study design and setting

2.1

This is a prospective, single-center, 8-week, double-blind, randomized, placebo-controlled clinical trial (NCT05560971) enrolling 40 individuals with a prediabetes and BMI of 25-40 kg/m^2^. Study participants will be recruited at Brigham and Women’s Hospital in Boston, Massachusetts, USA with the inclusion and exclusion criteria provided in **Table 1**. **Figure 2** shows a description of the enrollment and evaluation procedures. The protocol of this study was approved by the Institutional Review Board of Mass General Brigham. This investigator-initiated study is funded by Tersus Life Sciences, LLC, protocol no: 2022P001764.

**Table 1 T1:** Eligibility criteria.

**Inclusion Criteria**	Age 18 to 70 years with BMI 25-40 kg/m^2^
	Overweight and obese individuals with insulin resistance, prediabetes and/or impaired glucose tolerance HbA1c between 5.6-6.5, Impaired fasting plasma glucose (>99, ≤126 mg/dL), or HOMA-IR value above 2.5.
		BP <150/90 with or without medication, GFR>60, ALT, AST <300, TSH within normal ranges with or without medication
	**Exclusion Criteria**		Pregnancy or breastfeeding
			Use of any medications (except thyroid hormone with normal TSH, anti-hypertensives with blood pressure <150/90, and rescue inhalers for asthma)
		Use of OTC supplements (except vitamin D), avoiding supplements containing lipid supplements (e.g., fish oil macadamia oil, cod liver oil, krill oil, flaxseed, sea buckthorn oil) within 3 months of study participation is ensured	
Greater than 3 servings/day combined of cheese, milk, kefir, or yogurt for the last 3 months before the study	
Diagnosed with any type of diabetes mellitus and/or taking glucose-lowering medications	
Recent weight loss (more than 7% of TBW in last 3 months)	
Established major chronic diseases such as major cardiovascular disease (history of myocardial infarction, stroke, heart failure, coronary artery bypass graft, arrhythmia, peripheral arterial disease), bleeding disorder or anticoagulation use, active cancer, end-stage renal disease, proteinuria (>3g/day), dementia, severe chronic obstructive pulmonary disease (needs systemic steroid therapy), significant liver disease (ALT-AST>300)	
History of ongoing smoking cigarettes >1 pack/day, alcohol abuse, or drug abuse	
Treatment with any investigational drug in the one month preceding the study	

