### Subject enrollment

2.2

Participants will be recruited from the greater Boston area (using local news media, MBTA advertising, flyers, poster advertisements, brochure mailings, and online resources), Brigham and Women’s Hospital (using flyers), and the Mass General Brigham Health Care System (using Rally and Patient Gateway programs). Patient Gateway Research Invitations allow for direct communication with any eligible subjects who have not opted out of receiving Research Invitations. Additionally, potentially eligible participants who previously consented to be contacted about future research studies will be contacted (via email or phone).

Potential participants will undergo a 2-hour in-person screening visit to determine if they meet study eligibility requirements. Screening visit laboratory measurements are specified in **Table 2**. Written informed consent will be obtained during the screening visit by a licensed study physician. The screening visit will include a complete medical history and physical examination, laboratory studies (complete blood count, comprehensive metabolic panel, urine analysis, insulin, TSH, and a pregnancy test), and an electrocardiogram (EKG). Randomization to either POA supplement or placebo will be stratified based on BMI and biological sex and it will be done by the BWH Investigational Drug Pharmacy Service. The investigational agent (POA supplement) and placebo will be dispensed in a similar shape, size, color, and odor. For both POA and placebo, participants will be instructed to take 4 capsules daily: 2 capsules in the morning and 2 capsules in the evening before meals at consistent times each day. To facilitate timely medication intake, we send morning and evening reminder text messages to participants every day. Each 420 mg capsule of POA is 90% pure POA. Therefore, each capsule will contain 378 mg of POA, and the total amount of pure POA consumed per day in the treatment arm will be 1512 mg.

**Table 2 T2:** Screening visit tests.

Screening Visit Tests	
Blood Tests	Urine Tests
Complete Blood Count with differentials	Urinalysis, complete
Comprehensive Metabolic Panel	Urine Pregnancy Test
Hemoglobin A1c	EKG
TSH	
DNA Analysis	
Insulin	

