### Inpatient visits (Week 0 and Week 8)

2.4

Participants who qualify and decide to join the study will undergo two overnight study visits at week 0 and week 8 at Brigham and Women’s Hospital. After completing study procedures at week 0, participants will be given the study medication, either placebo or POA, and will be instructed to take 2 capsules twice a day. Laboratory measurements are shown in **Table 3**.

**Table 3 T3:** Admission tests.

Week 0 and Week 8 Assessments	
Admission Labs Day 0	Overnight Fasting Labs with Clamp Blood Sets
Urine HCG (Women)	Complete Blood Count with differentials
Potassium	Comprehensive Metabolic Panel
Hematocrit	Hemoglobin A1c, Insulin, C-Peptide, Glucagon, Cortisol, Melatonin
MMTT Day 0 (7 Hours Food Withdrawal)	hs-CRP, TNFa, IL-6
MMTT 0 Min-Glucose/C peptide	Total Adiponectin, Leptin
MMTT 30 Min-Glucose/C peptide	FABP4, NEFA, Glycerol
MMTT 60 Min-Glucose/C peptide	EDTA Extra Plasma, Extra Serum
MMTT 90 Min-Glucose/C peptide	RNA from PBMC
MMTT 120 Min-Glucose/C peptide	Lipid Panel, Essential Fatty Acid Panel, Direct LDL

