#### Sample size and power

2.6.2

The study is powered only for the primary endpoint, insulin sensitivity. We expect a mean insulin sensitivity-M value (measured as steady state clamp glucose infusion rate) of approximately 7.5 ± 1.7 mg/kg/min with placebo, based on previous clamp studies^30^. Based on previous human studies, we expect to see at least a 20% difference between placebo vs. POA treatments. A sample size of 40 subjects with complete data will provide greater than 80% power for these assumptions. We will perform stratified randomization based on subjects’ BMI (<30>), and gender for homogenous treatment groups. 3:2 POA vs placebo assignment will allow us to achieve this randomization goal. We were also implementing oral glucose tolerance test results for the additional stratification of the randomization, however additional invasive testing before starting the trial period caused scheduling conflicts and compliance problems. Hence, we have discontinued OGTT for the stratification criteria.

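### The tests named for the primary endpoint are paired before/after tests, which show change within an arm; no valid POA-versus-placebo test is specified as primary

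*Protocol article*

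**What the plan says.** The design is parallel-group. Section 2.1 of the protocol article says: "This is a prospective, single-center, 8-week, double-blind, randomized, placebo-controlled clinical trial". Section 2.4 says that after the week-0 procedures "participants will be given the study medication, either placebo or POA". No crossover is described. Section 2.6.2 gives 40 participants with complete data allocated 3:2, that is 24 on POA and 16 on placebo, and section 2.2 adds: "Randomization to either POA supplement or placebo will be stratified based on BMI and biological sex".

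The effect is defined between arms. In section 2.6.2 the expectation is that "we expect to see at least a 20% difference between placebo vs. POA treatments", against a placebo mean M of 7.5 with SD 1.7 mg/kg/min. Section 3.1 likewise expects POA to do better than placebo.

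The analysis in section 2.6.1 is framed within person. The primary-endpoint sentence reads: "We will use a paired t-test for the primary endpoint as we measure insulin sensitivity M and M/I values from the same individuals", and it goes on to refer to measurements before and after POA versus placebo. Because of the small sample, "we will also use Wilcoxon non-parametric test to compare two paired groups (before and after, POA vs placebo". The section then adds that "we will use multivariate regression analysis, which also provides the flexibility of controlling for and evaluating covariates such as age, sex, sleep, and BMI", and extends the same testing to every endpoint.

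**The concern.** Week-0 and week-8 values from one person form a pair. A POA recipient and a placebo recipient do not, and 24 people cannot be paired with 16. A paired t-test or signed-rank test therefore asks whether the mean or median change in one group differs from zero. It yields no estimate of the POA-minus-placebo difference, which is what randomisation protects and what the sample size assumes. The placebo arm would have no formal role in the primary test.

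Any change shared by both arms, such as familiarity with the clamp, trial participation, season or regression toward the mean, would enter the POA-arm result in full. Since the same testing applies to all endpoints, the problem carries over to liver fat, body composition, lipids and the inflammatory markers.

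**Working it through.** **Inputs from the document.** Placebo mean M 7.5 and SD 1.7 mg/kg/min, difference 20%, 40 completers, 3:2 allocation (all section 2.6.2). The difference is 0.20 × 7.5 = 1.5 mg/kg/min, with arms of 24 and 16.

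**Assumptions not in the document.** Two-sided alpha of 0.05; 1.7 read as a between-subject SD; week-0/week-8 correlation ρ of M between 0.5 and 0.8; common drift of 0, 2, 5 or 10% of 7.5, that is 0, 0.15, 0.375 or 0.75 mg/kg/min.

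**Step 1: the plan's own power figure (above 80%).** For a two-sample comparison the noncentrality is 1.5 / (1.7 × √(1/24 + 1/16)) = 1.5 / (1.7 × 0.3227) = 2.734.
- Normal approximation: Φ(2.734 − 1.960) = 78.1%.
- Noncentral t, 38 df: 75.9%. With 20 per arm it is 77.6%. Reaching 80% at 3:2 takes about 44 completers (26 and 18).
- One-sided 0.05, normal approximation: 86.2%.
- Paired test within the POA arm alone (n = 24): 83% at ρ = 0 and 98.5% at ρ = 0.5.

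The stated inputs thus come close to 80% for a between-arm test. Of the variants tried, only a one-sided test or a within-arm paired calculation exceeds it. The article does not say which was used.

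**Step 2: what the paired test does when POA has no effect.** The SD of change is 1.7 × √(2(1 − ρ)): 1.700, 1.317 and 1.075 at ρ = 0.5, 0.7 and 0.8. The noncentrality is drift × √24 / SD of change. For example, at ρ = 0.7 and 5% drift it is 0.375 × 4.899 / 1.317 = 1.395. The chance that the POA-arm paired t-test (23 df) is significant is:

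| Common drift | ρ = 0.5 | ρ = 0.7 | ρ = 0.8 |
|---|---|---|---|
| 0% | 5% | 5% | 5% |
| 2% | 7% | 8% | 10% |
| 5% | 18% | 27% | 37% |
| 10% | 54% | 76% | 91% |

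A common drift cancels in a between-arm contrast. In simulation (40,000 trials per setting, drifts of 0, 5, 10 and 20%), a two-sample t-test on change rejected in 4.8 to 5.1% of trials throughout.

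**Step 3: power of a valid between-arm test for 1.5 mg/kg/min at 24:16.** ANCOVA replaces 1.7 by the approximate residual SD 1.7 × √(1 − ρ²). At ρ = 0.5 that is 1.472, and the noncentrality is 1.5 / (1.472 × 0.3227) = 3.157.

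| Analysis | ρ = 0.5 | ρ = 0.6 | ρ = 0.7 |
|---|---|---|---|
| t-test, week-8 M only | 76% | 76% | 76% |
| t-test, change in M | 76% | 85% | 93% |
| ANCOVA, baseline M (37 df) | 87% | 91% | 96% |

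Spending two more degrees of freedom on the strata lowers the ANCOVA figures by about 0.1 point.

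**The case against.** A reader might infer that the randomised comparison is never tested. The document does not support that. Section 2.6.1 refers twice to POA versus placebo, wants to look at sex differences in the POA effect, and plans a regression that could carry a treatment term. A comparison between arms is evidently intended, and the article condenses a fuller protocol. This limits the claim but does not remove it: the article does more than leave the test open. It names a paired test, gives a reason for it, and describes POA and placebo as paired groups, which they are not. An analysis plan that followed it would inherit the error.

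Three further readings do not hold:
- **Covariates.** That baseline M is absent from the regression list is not an error. The list is given as examples, and it already contains BMI and sex, the two stratification factors. Model detail of that kind commonly belongs to the analysis plan.
- **Diet as the source of drift.** Section 2.3 starts the restriction two weeks before week 0, so both clamps fall under it and only a residual effect could reach the week-0 to week-8 change. On the trial's own hypothesis, removing POA would lower insulin sensitivity, not imitate a benefit. Regression toward the mean after selection on glycaemic criteria is possible, but its size is unknown.
- **Separate significance in each arm.** The protocol nowhere says it will claim an effect when POA is significant and placebo is not. No error rate for that rule can be charged to it.

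The error rates for the POA-arm test also depend on assumed drift. With no drift that test keeps its 5%.

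**Conclusion.** Wrong as written. The tests named for the primary endpoint cannot estimate the difference between POA and placebo on which the hypothesis and sample size rest, and the one method that could do so is neither specified nor made primary. This conclusion needs no numerical assumption; it follows from the parallel design and the paired test.

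The possible damage does depend on assumptions. It is negligible without common drift, modest at 2%, and at 5% or more the POA-arm false-positive rate is at least three times the nominal 5%. The document gives no information on which drift or correlation applies, so the figures are illustrative. The matter should be settled before analysis because the primary conclusion depends on it.

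**What to change.** In section 2.6.1, replace the primary test with a between-arm ANCOVA: week-8 clamp M on randomised arm, week-0 M, BMI stratum and sex, reporting the adjusted POA-minus-placebo difference with a 95% confidence interval and a two-sided p-value. Use a Wilcoxon rank-sum test on change, between arms, as the non-parametric sensitivity analysis. Keep the paired within-arm tests as descriptive only, and apply the same approach to the other endpoints. Section 2.6.2 should then restate power for this test at 3:2, with alpha, sidedness and the assumed correlation.

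What is essential is that one between-arm test be named as primary. A two-sample test on change would also hold the error rate; ANCOVA is preferred for its power. The cost is wording only: the clamps at weeks 0 and 8 are already scheduled, and BMI and sex are already recorded for randomisation.

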### Palmitoleic acid-free diet

2.3

Two weeks before Inpatient Visit 1 (Week 0), enrolled participants will be asked about their dietary habits and exercise routine. Afterwards, they will be instructed not to change their dietary and exercise habits intentionally except for eliminating foods known to contain large amounts of POA from their diet until after the entire study is complete. These foods are sardines, menhaden, anchovies, pollock, herring, macadamia nuts, sea buckthorn oil, krill oil, cod liver oil, and macadamia nut oil. Also, they will be limiting their dairy intake to no more than 1 total dairy serving a day. Our goal is to eliminate any residual effect of POA present in participants’ regular diets and to improve the detection of the acute effects of POA. With the exception of having participants avoid POA rich foods, we aim to achieve a real-life experience with no dietary or exercise coaching. Additionally, participants will be abstinent from activities that alter insulin sensitivity the day before the inpatient visits such as drinking any alcohol, consuming caffeine, and performing strenuous exercise.

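### The primary test is a paired test, but POA and placebo values come from different people, so it cannot make the between-arm comparison that the trial is designed for

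*Protocol article*

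**What the plan says.** Protocol article, section 2.6.1 (Statistical methods), names the primary analysis and gives its reason: "We will use a paired t-test for the primary endpoint as we measure insulin sensitivity M and M/I values from the same individuals before". The sentence goes on to the value after treatment and mentions both treatments. Because normality may fail in a small sample, the section adds a "Wilcoxon non-parametric test to compare two paired groups (before and after, POA vs placebo". It then says "we will use multivariate regression analysis, which also provides the flexibility of controlling for and evaluating covariates such as age, sex, sleep, and BMI", and extends the same testing to all endpoints.

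The design is set out elsewhere in the article:

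- Section 2.2: "Randomization to either POA supplement or placebo will be stratified based on BMI and biological sex".
- Section 2.4: participants "will undergo two overnight study visits at week 0 and week 8".
- Section 2.6.2: allocation is 3:2, the expected placebo M value is 7.5 ± 1.7 mg/kg/min, and "we expect to see at least a 20% difference between placebo vs. POA treatments". Forty completers are said to give more than 80% power.
- Section 3.1: the expected result is an improvement with POA relative to placebo.

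**The concern.** A paired test needs two measurements on the same unit. In this trial the pairs are week 0 and week 8 in one person. POA and placebo are taken by different people in groups of unequal size, so there is nothing to pair across arms. Taken literally, the primary t-test and its Wilcoxon back-up each answer whether insulin sensitivity changed in an arm. They do not answer whether it changed more on POA than on placebo.

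A within-arm change is the sum of any treatment effect and anything else that moved between the two visits. The placebo arm exists to separate the two, and a within-arm test does not use it. Noting that one arm reached significance and the other did not is no substitute, because the arms differ in size and so in power. Since the same testing is extended to all endpoints, the problem reaches the secondary results too.

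**Working it through.** **1. Question against test.**

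| Element | Where | Type of comparison |
|---|---|---|
| Expected result | 3.1 | POA against placebo |
| Effect used for power | 2.6.2 | POA against placebo |
| Treatment received | 2.2 | One per person |
| Primary t-test | 2.6.1 | Paired, before and after |
| Wilcoxon back-up | 2.6.1 | Paired |
| Regression | 2.6.1 | Covariates listed, no arm term named, not designated primary |

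No two-sample test is named anywhere.

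**2. Which test does the stated power describe?** Inputs from 2.6.2: difference 20% × 7.5 = 1.5; SD 1.7; 40 completers at 3:2, so 24 and 16. Two-sided 5% is assumed, because the section gives no significance level.

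- Two-sample comparison: noncentrality = 1.5 / (1.7 × √(1/24 + 1/16)) = 2.73. Power is 78.1% by the normal approximation and 75.9% by the t distribution (38 df).
- At 20:20 the figures are 79.7% and 77.6%.

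The stated figure of more than 80% is thus close to a two-sample calculation, though slightly above it when two-sided. The power statement describes a between-arm test, which is not the test named in 2.6.1.

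**3. What a common change would do to the paired test.** This is an illustration. The week 0 to week 8 correlation r and the common drift are assumptions; the documents give neither.

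- SD of change = 1.7 × √(2(1 − r)). At r = 0.5 this is 1.7.
- No POA effect, both arms rise by 10% of 7.5 = 0.75. POA arm: noncentrality = 0.75 / (1.7/√24) = 2.16, 23 df, critical value 2.07. The probability of a significant improvement is 54%. Placebo arm (n = 16): 0.75 / (1.7/√16) = 1.76, giving 38%.
- POA significant and placebo not: 0.544 × (1 − 0.379) = 34%. The reverse: 0.379 × (1 − 0.544) = 17%.
- Common rise of 5% (0.375): 18% in the POA arm and 13% in placebo. POA only 15%, placebo only 11%.
- Range over r for the POA arm at a 10% rise: 42% at r = 0.3 and 91% at r = 0.8.
- No drift: 2.5% for a false improvement, which is the nominal rate.
- Common fall of 5%, no POA effect, r = 0.5: 0.14%.
- Common fall of 10% with a true POA effect of 1.5, r = 0.5: the net change in the POA arm is 1.5 − 0.75 = 0.75, so improvement is detected 54% of the time, against 98.5% without the fall.

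**4. Is a between-arm test feasible with 40 completers?** Difference 1.5, 24:16, two-sided 5%, t distribution. The ANCOVA figures are approximate and use residual SD = 1.7 × √(1 − r²).

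| r | Two-sample t on change | ANCOVA with baseline |
|---|---|---|
| 0.3 | 61% | 80% (79.8%) |
| 0.5 | 75.9% | 86.8% |
| 0.8 | 98.8% | 99.3% |

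An unadjusted two-sample t-test on week 8 values has 75.9% power whatever r is.

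**The case against.** The strongest reply is that a between-arm comparison was plainly intended. Section 2.6.1 mentions both treatments in its t-test and Wilcoxon sentences, sections 2.6.2 and 3.1 are explicitly comparative, and the promised regression would naturally carry a treatment term. The article nowhere says that efficacy will be concluded from a within-arm p-value. This stands as evidence of intent, and it makes the consequence less certain. It does not repair the text: a paired test cannot deliver that comparison, and the regression neither names an arm term nor is made the deciding analysis. An analysis plan that is not shown may say more, but the article states a specific test with a reason rather than leaving the choice open.

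Two stronger readings are tempting, and the documents do not support them.

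- **That shared drift will be reported as a POA benefit.** No section gives any drift. The diet change that might suggest one, in which "they will be limiting their dairy intake to no more than 1 total dairy serving a day" and POA-rich foods are avoided, begins two weeks before week 0, so part of its effect may already be in the baseline. Other diet and exercise habits are to stay as they were. On the trial's own hypothesis, removing dietary POA would lower insulin sensitivity in both arms, which would hide a benefit rather than create one. The daily messages concern taking the capsules, and nothing suggests that repeating the clamp raises M.
- **That 3:2 allocation makes the error favour POA only.** It gives a tilt: 34% against 17% at a 10% common rise, and only 15% against 11% at 5%.

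**Conclusion.** The point holds as a mismatch between test and question: the primary test as written, and its back-up, cannot compare POA with placebo in this design. That conclusion follows from the article's own description and depends on no assumed number. It should be corrected before analysis, because it concerns the primary endpoint and is carried to all the others.

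The size of the consequence is not known. The rate of false improvement in the POA arm is 54% for a 10% common rise at correlation 0.5 (42% to 91% for correlations 0.3 to 0.8), is nominal with no drift, and falls well below nominal with a common fall. These figures show sensitivity in either direction and are not a forecast. They rest on SD 1.7 from section 2.6.2 and on assumed drift and correlation.

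**What to change.** In section 2.6.1 and the analysis plan:

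- Name one primary test: a between-arm ANCOVA of week 8 clamp insulin sensitivity on treatment arm, adjusted for the baseline value, BMI stratum and sex, at two-sided 5%. Report the POA minus placebo difference with its 95% CI. Say which clamp measure this is, since 2.6.1 lists both M and M/I while the power is stated for M.
- As the non-parametric back-up, use the rank-sum (two-sample) Wilcoxon test on individual week 8 minus week 0 changes.
- Present within-arm changes descriptively, and apply the same rule to the other endpoints.

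In section 2.6.2, state the power for this ANCOVA together with its assumed correlation: about 80% at 0.3 and 87% at 0.5 for 24:16, against 75.9% for an unadjusted two-sample t-test. At 0.3 the figure is marginally under 80%, so the present claim of more than 80% depends on the correlation chosen.

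The cost is a few sentences. No new measurements are needed, and no more participants if a correlation somewhat above 0.3 is credible. The downside is that between-arm p-values will usually be less favourable than within-arm ones.

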### Pitfalls and alternative approaches

3.3

This is an 8-week clinical trial, and the duration might not be sufficient to observe the beneficial effects of POA on insulin sensitivity. Because other studies demonstrate the effects of POA on metabolism after 1 month, we decided to limit the study timeframe to 8 weeks to make sure patient compliance is established (27, 47). The study is powered for the insulin sensitivity measured with the gold standard method of the hyperinsulinemic-euglycemic clamp. Therefore, 40 participants may not be adequate to exhibit statistically significant differences in secondary endpoints being liver fat mass, total body fat mass, body fat composition, glucose and c-peptide levels post-mixed meal, serum glucose, insulin, c-peptide, liver function tests, fasting lipid panel, hs-CRP, circulating inflammatory cytokines (TNF-a, IL1-B, IL-6), FABP4, glucagon, POA, free fatty acids, glycerol, adiponectin, leptin measurements. Additional studies designed to focus on secondary endpoints might be necessary to show significant effects. We aim to select participants who has insulin resistance via using criteria identifies individuals with overweight-obesity and prediabetes. However, we might still get participants with high insulin sensitivity, where there might not be enough therapeutic window to improve. In that case, we might need to add more strict inclusion and/or exclusion criteria or randomize potential insulin sensitive participants equally to treatment arms.

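### The paired before/after tests set for all endpoints cannot use the week 4 fasting values, so for HOMA-IR and most serum markers a participant lost after week 4 drops out of those tests

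*Protocol article*

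**What the plan says.** Section 2.6.1 sets the primary test: "We will use a paired t-test for the primary endpoint as we measure insulin sensitivity M and M/I values from the same individuals". It adds a rank test: "we will also use Wilcoxon non-parametric test to compare two paired groups (before and after, POA vs placebo". It also says that "we will use multivariate regression analysis, which also provides the flexibility of controlling for and evaluating covariates such as age, sex, sleep, and BMI", without stating which visits that regression uses. It then extends the methods: "We will apply the same testing to all endpoints".

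Section 2.4 places the inpatient assessments at "two overnight study visits at week 0 and week 8". Section 2.5 adds a third visit: "After four weeks on the study medication, participants will come to the Center for Clinical Investigation (CCI) for a blood draw". Table 5 shows that this fasting draw covers:

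- insulin, C-peptide and glucagon
- a metabolic panel (hence glucose and liver tests) and lipids
- hs-CRP, TNFa and IL-6
- adiponectin, leptin, FABP4, NEFA and glycerol

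Table 6 lists these as secondary endpoints and places HOMA-IR, which needs only fasting insulin and glucose, within the primary endpoint. No section says how the week 4 values enter the analysis, and none says that they are left out.

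**The concern.** A paired t-test or a paired Wilcoxon test uses two values per person and omits anyone who lacks one of them. The plan assigns these tests to endpoints measured three times. If the second value is week 8, a participant who gives blood at week 4 and is then lost adds nothing to the tests of HOMA-IR or the serum markers.

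Two things are at stake. If loss after week 4 is related to the week 4 result and differs between arms, the completers are a selected group and the POA-placebo difference is distorted. If loss is random, some precision goes unused in a 40-person trial whose authors accept in section 3.3 that the secondary endpoints may be underpowered. The same section justifies the trial's length with "Because other studies demonstrate the effects of POA on metabolism after 1 month", so on the authors' own reasoning a week 4 value should carry information about response.

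**Working it through.** **The plan's own figure.** Section 2.6.2 gives a mean of 7.5, an SD of 1.7, a 20% difference (0.20 x 7.5 = 1.5) and 3:2 allocation of 40 (24 and 16). Alpha is not stated; I assume 0.05 two-sided.

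- Standard error = 1.7 x sqrt(1/24 + 1/16) = 0.549.
- 1.5/0.549 = 2.73; less 1.96 = 0.77; power is about 78%.

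This is close to the stated figure of more than 80% (one-sided it is 86.2%). It concerns the clamp M value, which has no week 4 measurement, so nothing below disputes it.

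**Which endpoints are affected.** Comparing Table 6 with Table 5:

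- Also measured at week 4: HOMA-IR, fasting glucose, insulin, C-peptide, liver tests, lipids, hsCRP, TNFa, IL-6, FABP4, glucagon, free fatty acids, glycerol, adiponectin, leptin.
- Not listed at week 4: clamp M and M/I, MRI-PDFF, DEXA, mixed-meal test, POA, cortisol, IL1-B.

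**Bias within one arm.** The documents give no dropout rate or correlation, so these are assumed ranges. Let rho be the week 4 to week 8 correlation given baseline.

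- If the worst fraction p at week 4 leaves, completer bias = rho x phi(z_p)/(1 - p), where phi is the normal density at the p-quantile.
- For p = 0.20: 0.280/0.80 = 0.35, giving 0.18 SD at rho 0.5 and 0.24 SD at rho 0.7.
- In a milder case, the odds of leaving double per SD worse at week 4. Simulation gives 0.02, 0.03 and 0.06 SD at rho 0.5, and 0.02, 0.04 and 0.09 SD at rho 0.7, for 5%, 10% and 20% dropout.

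This reaches the arm comparison only as far as dropout differs between arms.

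**Bias in the arm comparison.** Simulation with 24 vs 16, a true effect of 0.5 SD and between-visit correlations of 0.5 to 0.8. Assumed loss: 5 of 24 POA (21%) weighted to poor week 4 change, and 1 of 16 placebo (6%) at random. The covariance is estimated, not taken as known.

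| Analysis | Error in the effect |
|---|---|
| Completer change score | +15 to +23% (0.15 x 0.5 = 0.075 SD to 0.23 x 0.5 = 0.115 SD) |
| Completer ANCOVA | +10 to +14% (0.05 to 0.07 SD) |
| Model with weeks 0, 4 and 8 | within 3% |

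**Precision under random loss of 6 of 40 (34 complete).** Let r be the common correlation between visits.

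- Change-score variance is 2(1 - r); baseline-adjusted variance is 1 - r^2. The ratio is (1 + r)/2: 0.75 at r = 0.5 and 0.90 at r = 0.8, so 25% to 10% lower from baseline adjustment alone.
- Given baseline, rho = r/(1 + r) = 0.333 to 0.444. Adding week 4 lowers the variance by a further rho^2 x (1 - 34/40): 0.111 x 0.15 = 1.7% to 0.198 x 0.15 = 3.0%.
- Together: 1 - 0.75 x 0.983 = 26% at r = 0.5, and 1 - 0.90 x 0.970 = 13% at r = 0.8.

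These are large-sample values with known covariance. With the covariance estimated, simulation gives about 8-23% against change scores and 1-3% against ANCOVA. Most of the gain is therefore baseline adjustment.

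**The same in participants.** The variance of the week 8 mean is proportional to (1 - rho^2)/n_complete + rho^2/n. At 10% loss and rho 0.5: 0.75/36 + 0.25/40 = 0.02708, an effective 36.9 against 36. Over 5-20% loss and rho 0.5 to 0.7, the recovery is about 0.5 to 3.5 participants.

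**The case against.** The strongest reply is that this is a condensed article. Analysis sets, missing-data rules and the use of interim visits usually sit in the full protocol or SAP, which are not shown, so silence on them is no fault. That is right, and the absence of a missing-data rule is not the point here. The point is what section 2.6.1 does fix: a two-value test, extended to all endpoints. A later plan would have to depart from that text to use three visits.

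A regression is also named, and it precedes the sentence about all endpoints. It is introduced for covariates with no visit structure, so it could accommodate week 4 but does not say so. Nor is the second measurement explicitly tied to week 8 for the serum endpoints. Week 8 is only the natural reading, because the clamp, for which the test is written, exists only at weeks 0 and 8.

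On size, the 15-23% rests on a chosen dropout pattern. With 5-10% dropout and the milder mechanism, the within-arm bias is 0.02 to 0.04 SD, and it cancels if both arms lose people alike. This stands.

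A reader might infer more than the text supports:

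- That every paired test loses collected data. It does not: clamp, MRI, DEXA, mixed-meal, POA, cortisol and IL1-B have no listed week 4 value to lose.
- That the week 4 visit is wasted. The blood count and metabolic panel may also serve monitoring, and the document does not exclude the values from analysis.
- That only completers form the analysis set, from "A sample size of 40 subjects with complete data will provide greater than 80% power for these assumptions". That sentence is a power assumption.
- That stopping capsules means a missing week 8 value. Nothing says so; the issue is participants without week 8 data.

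**Conclusion.** The point holds for HOMA-IR and the serum endpoints drawn at weeks 0, 4 and 8. The stated paired tests cannot use the week 4 value, and on the week 8 reading they omit anyone lost after week 4. The bias could be material: about 15-23% for completer change scores and 10-14% for completer ANCOVA, if dropout is unequal and related to week 4 response as assumed. It is small if dropout is low or similar in the two arms. The three-visit model removes it when dropout depends only on observed values. The precision gain from week 4 itself is minor, 1-3% beyond baseline adjustment. The powered clamp measure is untouched. This is a worthwhile improvement to the analysis of mainly unpowered endpoints and does not threaten the trial's main result.

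**What to change.** In section 2.6.1, for HOMA-IR and each serum endpoint measured at weeks 0, 4 and 8, replace the paired t-test and Wilcoxon test with a likelihood-based repeated-measures model:

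- Include baseline, visit, arm-by-visit and the randomisation strata (BMI at the cut of 30, sex).
- Analyse all randomised participants in their assigned arm, using whatever visits they have.
- Name the POA-placebo difference at week 8 as the result.
- Log-transform skewed markers such as hsCRP and the cytokines, which meets the normality worry behind the Wilcoxon test.
- Use a small-sample degrees-of-freedom correction such as Kenward-Roger.

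The regression already named in that section could be specified as this model. The change does not affect clamp, MRI, DEXA, mixed-meal, POA, cortisol or IL1-B endpoints.

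The cost is analysis wording only, with no new visit, sample or participant. The downside is slightly more modelling and a missing-at-random assumption in a 40-person trial.
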